### Outcome measures and assessment procedures

Telephone interviews aim to identify changes in functional class or clinical events taking place over the follow-up period.

The final 12-month interview will evaluate the same components assessed in the initial interview, in order to determine improvement/worsening of clinical status. All patients will undergo blood tests with serum lipids and glucose evaluation.

The primary outcome is maintenance of CCS I or II at 12 months.

Secondary outcomes focus on risk factors. Control of risk factors will analyze variations of at least 5 % in the following pre and post-intervention measurements [12]:systemic blood pressure;controlled dyslipidemia: LDL < 100 mg/dL;glycated hemoglobin (in the presence of diabetes);abstinence from tobacco smoking;about 150 min/week of regular physical activity.

Additional secondary outcomes include health care access variables, such as: medical appointment in primary care facility taking place within not more than six months after referral, with review of medications and issue of prescriptions; and disease instability during the 12-month follow-up, defined as the need for seeking emergence care due to cardiovascular disease: acute chest pain; heart failure decompensation; acute arrhythmias; stroke.

Given the objective nature of the outcomes, the safety of the intervention, and the brief follow-up period, endpoint adjudication and data monitoring committees will not be appointed. No interim analyses are proposed. At the 4 and 8-month telephone interviews patients will be asked about possible unintended effects of the trial, and will receive guidance as required. After the trial, patients will be readmitted to the outpatient clinic if continued care at a primary care facility is not available.

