**Methods/design:**

We designed a randomized non-inferiority protocol that will include 280 patients with stable coronary artery disease (for at least 12 months). Patients will be selected from the Ischemic Heart Disease Clinic in a tertiary care hospital in southern Brazil. Enrolled participants will be randomized into one of two groups: 12 months of follow-up at the same clinic; or 12 months of follow-up at a primary care facility with clinical support from a telemedicine platform including a toll-free line for physicians (intervention group). In the intervention group, decisions to refer patients to tertiary care during follow-up will be made jointly by primary physicians and medical teleconsultants. The groups will be compared in terms of the primary outcome—maintenance of baseline functional class 1 or 2 after 12 months. Secondary outcomes include control of risk factors and instability of the disease.

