### Study population and sample size

The study population will be selected among patients from the Ischemic Heart Disease outpatient clinic at HCPA, a tertiary care university hospital in South Brazil. All clinic patients have CAD defined by the presence of at least one of the following: documented history of myocardial infarction, surgical or percutaneous myocardial revascularization, lesion > 50 % in at least one coronary artery assessed by angiography, or presence of angina and positive noninvasive testing of ischemia [8].

Study participants will undergo standard anamnesis and medical examination to verify clinical stability and discharge criteria.

The sample size was calculated as 140 patients in each group—considering a non-inferiority margin of 10 % and incidence of 92 % of the main outcome, that is, maintenance of Canadian Cardiovascular Society Functional Classification (CCS) 12 months after the start of follow-up. This was based on the rate of patients with increase in angina to a higher CCS reported by a previous study for the control group receiving optimal treatment for CAD [9]. An additional 10 % margin was added to account for losses to follow-up. For calculation of sample size, a ß of 0.9 and an α of 0.05 (two-sided) were considered.

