### Inclusion and exclusion criteria

Individuals of both genders, aged ≥ 18 years, with a diagnosis of CAD and CCS I or II at the moment of enrollment, without cardiovascular events requiring hospital admission during the previous year, will be selected for the study. Verification of discharge criteria will be performed by the medical team running the clinic, without interference from the investigators.

Patients who have been followed-up at the clinic for less than 1 year, unstable patients needing medication adjustments, patients performing diagnostic evaluation at the moment of enrollment, or those who do not agree with the outcome of randomization will be excluded.

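### The primary outcome, read plainly, counts a move from CCS I to II as success, whereas the 92% behind the sample size counts it as failure

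*Protocol article*

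**What the plan says.** All references are to the protocol article.

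- **Outcome measures and assessment procedures:** "The primary outcome is maintenance of CCS I or II at 12 months".
- **Inclusion and exclusion criteria:** patients are enrolled "with a diagnosis of CAD and CCS I or II at the moment of enrollment". The share in each class is not given.
- **Study population and sample size:** the calculation was made "considering a non-inferiority margin of 10 % and incidence of 92 % of the main outcome", and the main outcome is described there as "maintenance of Canadian Cardiovascular Society Functional Classification (CCS) 12 months after the start of follow-up", without the words I or II. On the source of the 92%: "This was based on the rate of patients with increase in angina to a higher CCS reported by a previous study", namely its optimally treated control group.
- **Abstract, Methods/design:** the primary outcome is "maintenance of baseline functional class 1 or 2 after 12 months".

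**The concern.** Two rules for the primary outcome stand in the same document, and they classify one kind of patient in opposite ways. A patient who enters in class I and is in class II at 12 months is within CCS I or II, so the outcomes section on its plain reading records a success. The same patient has risen to a higher class, so the basis of the 92% records a failure.

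The expected rate, the sample size and the meaning of the margin all follow from the second rule, while the outcome as defined follows the first. In a non-inferiority trial this matters because a fixed absolute margin becomes more permissive, relative to control, as failure becomes rarer. The endpoint would also not register I-to-II worsening in either arm.

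**Working it through.** **Step 1. The plan's own figure.** Inputs from the sample size section: success p = 0.92 (taken as equal in both arms), margin 0.10 (taken as absolute), 10% for losses, and "a ß of 0.9 and an α of 0.05 (two-sided) were considered". The 0.9 is read as power 0.90.

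Formula: n per group = 2p(1−p)(z_alpha + z_power)² / margin².

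- One-sided alpha 0.05: 2 × 0.92 × 0.08 × (1.6449 + 1.2816)² / 0.01 = 14.72 × 8.564 = 126.1, so 127. Allowing for losses, 127 × 1.1 = 139.7 (140) or 127 / 0.9 = 141.1 (142). This reproduces 140.
- Two-sided 0.05 as written (one-sided 0.025): 14.72 × 10.508 = 154.7, so 155, then 171 (× 1.1) or 173 (/ 0.9). This does not reproduce 140.

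So 140 rests on 92% success, a 10-point margin and one-sided 0.05. The labelling of alpha is a separate matter. One-sided 0.05 is used below so that only the endpoint changes.

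**Step 2. How the two rules relate.**

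| Entry class | Class at 12 months | CCS I or II | No rise above own baseline |
|---|---|---|---|
| I | I | success | success |
| I | II | success | **failure** |
| I | III or IV | failure | failure |
| II | I or II | success | success |
| II | III or IV | failure | failure |

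Failures under CCS I or II are a subset of failures under no rise. In the same patients, success under CCS I or II is therefore at or above success under no rise.

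**Step 3. What the margin then permits.** The 92% implies that 8% rise in class. The share of these who move only from I to II is not given. **Assumption:** 25%, 50% or 75%. Control failure q is then 0.08 × (1 − share).

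- Tolerated failure ratio = (q + 0.10) / q.
- Power with 140 × 0.9 = 126 evaluable per arm = Φ(0.10 / √(2p(1−p)/126) − 1.6449).

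| Assumed I-to-II share | Success | Failure in control, and at the margin | Ratio | Power |
|---|---|---|---|---|
| 0 (planning basis) | 92% | 8%, 18% | 2.25 | 90.0% |
| 25% | 94% | 6%, 16% | 2.67 | 95.5% |
| 50% | 96% | 4%, 14% | 3.5 | 99.2% |
| 75% | 98% | 2%, 12% | 6.0 | >99.9% |

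**Step 4. What holding the ratio would take.** Keeping the tolerated ratio at 2.25 means a margin of 1.25q: 7.5, 5 or 2.5 points. By the formula in Step 1, with power 0.90, one-sided 0.05 and division by 0.9 for losses, n per group would be 192, 294 or 598. This shows how much work the 10-point margin does; it is not a proposed sample size.

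**The case against.** **The reading of the outcome is not forced.** No sentence says that a move from I to II is a success. The outcome can be read as each patient keeping his or her own class, and the final interview is meant to establish whether the patient has got better or worse. This stands as a limit on certainty: the conflict lies between the plain reading of one section and the stated basis of another. A reader might infer that the abstract settles the matter in favour of the patient's own class. It does not; its wording fits either reading.

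**CCS I or II is a coherent endpoint.** It mirrors the entry criterion and asks whether patients stay within the range that made them eligible. This also stands. The fault is the mismatch with the planning basis, not the choice of that endpoint.

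**The size is assumed.** Neither the mix of classes at entry nor the share of I-to-II moves is given. If nearly all patients enter in class II, the two definitions almost coincide. Nor do the documents support calling I-to-II the commonest deterioration.

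Two stronger readings are tempting and are not supported:

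- A reader might infer that the trial is underpowered, since 126 per arm at 92% and one-sided 0.025 gives 83%. The gap from 90.0% comes wholly from the labelling of alpha. At a fixed margin the endpoint mismatch raises power.
- A reader might infer that deaths would be censored or left out, because one secondary outcome is "disease instability during the 12-month follow-up, defined as the need for seeking emergence care due to cardiovascular disease" and its listed presentations do not include death. The statistical analysis section does not define the events in its event-free survival analysis or tie them to that outcome. How death enters a symptom endpoint is commonly left to the full protocol or SAP, neither of which is shown.

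**Conclusion.** The point holds as an unreconciled mismatch between the primary outcome as defined and the event behind its planning rate. That the mismatch exists follows from the text. Its direction follows from the subset argument: success under CCS I or II cannot be lower than under no rise in class in the same patients.

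Its size rests on assumption. Over the assumed 94% to 98% success, the 10-point margin would accept between 2.67 and 6.0 times the control failure rate, against 2.25 times on the planning basis. The range presumes that the 8% rise rate applies to this population and that the margin is absolute. The cost falls on the strictness and content of the non-inferiority claim, not on power. It should be settled, because one kind of patient changes sides according to the rule applied, and a choice made after outcome data are seen could look data-driven.

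**What to change.** Before outcome data are seen, state one definition of the primary outcome and use it in the abstract, the sample size section and the outcomes section. Either option resolves the conflict:

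1. **CCS class at 12 months no higher than the patient's own baseline class** (I stays I; II stays II or improves to I). This matches the basis of the 92%, so the rate and margin can stand on their present footing. Report CCS I or II as a secondary outcome. The small downside is that a one-grade change now counts, which is noisier. Making survival part of the definition would be a further change: the 92% is described by angina class alone, so the expected rate would then need restating.
2. **Keep CCS I or II.** Restate the expected success rate for that endpoint, say what failure rate in the intervention arm the 10-point margin then permits, justify that margin, and recompute the sample size.

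The cost is a wording amendment, plus a recalculation under option 2. CCS class is already collected at baseline and at 12 months, so neither option needs new data.

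### The single 5 % variation rule for risk-factor control has no direction, is undefined for tobacco abstinence and conflicts with the LDL target, so it does not define a usable secondary endpoint

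*Protocol article*

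**What the plan says.** In the protocol article, Outcome measures and assessment procedures, the risk-factor outcomes are introduced by one sentence: "Control of risk factors will analyze variations of at least" 5 % "in the following pre and post-intervention measurements". Five items follow:

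- "systemic blood pressure", with no target and without saying systolic or diastolic;
- "controlled dyslipidemia: LDL" below 100 mg/dL;
- "glycated hemoglobin (in the presence of diabetes"), with no target;
- "abstinence from tobacco smoking";
- about 150 "min/week of regular physical activity".

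The sentence does not say whether a rise or a fall counts, whether 5 % is relative or in percentage points, or whether it refers to a patient or to a group. The Statistical analysis section names logistic regression for the effect of the strategy on primary and secondary outcomes at 12 months. It also lists the t-test or Wilcoxon's test for comparing continuous variables between groups.

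**The concern.** Logistic regression needs a yes/no event for each patient. The only threshold offered across the five items is the 5 % variation, so a reader following the text would code the event from it. That coding treats improvement and deterioration alike, cannot be carried out for one item, and contradicts the stated target for another.

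The trial asks whether follow-up in primary care is as good as follow-up in the tertiary clinic. If worsening counts the same as improvement, an arm whose risk factors deteriorate can show the same event rate as an arm whose risk factors improve. Risk-factor results would then be hard to interpret in exactly the situation where they are needed.

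**Working it through.** The protocol derives no sample size, power or error rate from the 5 % rule, so there is no figure of its own to reproduce. The check takes the rule item by item.

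**1. Direction.** The condition as written is |change| ≥ 5 %. With symmetric measurement error, the probability of meeting it is the same for a true change of +d as for −d. Two arms moving by equal amounts in opposite directions would have equal event rates.

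**2. Tobacco abstinence.** Code it 0 or 1 in one patient. From 0, a relative change is a division by zero. From 1, it is either 0 % or −100 %. A 5 % cut separates nothing.

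**3. LDL.** The value is continuous, so 5 % can be computed, but it disagrees with the target of < 100 mg/dL:

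| LDL before → after (mg/dL) | Relative change | Meets 5 % rule | Below 100 at 12 months |
|---|---|---|---|
| 103 → 99 | −4/103 = −3.9 % | no | yes |
| 160 → 150 | −10/160 = −6.25 % | yes | no |
| 90 → 98 | +8/90 = +8.9 % | yes, as a worsening | yes |

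In general, any patient starting between 100 and 100/0.95 = 105.3 mg/dL can reach the target with a fall of less than 5 %.

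**4. Physical activity.** The same conflict arises if minutes are recorded: a patient starting above 150/1.05 = 142.9 min/week can reach 150 with a rise of less than 5 %.

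**5. Blood pressure, if the rule is applied per patient.** The documents give no variability, so the inputs are assumptions: mean systolic pressure 135 mmHg, within-person SD s of 7 to 12 mmHg per measurement, independent normal errors, no true change.

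- Threshold: 0.05 × 135 = 6.75 mmHg.
- SD of change: √2 × s.
- P(|change| ≥ 6.75) = 2 × [1 − Φ(6.75/(√2 × s))].

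| s (mmHg) | SD of change | Either direction | Fall only |
|---|---|---|---|
| 7 | 9.90 | 0.495 | 0.248 |
| 10 | 14.14 | 0.633 | 0.317 |
| 12 | 16.97 | 0.691 | 0.345 |

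The result depends strongly on the assumption. Written with a within-person coefficient of variation c, the either-direction probability is 2 × [1 − Φ(5/(√2 × c))]: 1.8 % at c = 1.5 %, 7.7 % at 2 %, 23.9 % at 3 %, 48.0 % at 5 % and 72.4 % at 10 %. A 5 % change falls inside the 95 % noise band once c exceeds 5/(1.96 × √2) = 1.8 %, which is about 2.4 mmHg at 135 mmHg.

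**The case against.** The strongest reply is that the outcome is called control of risk factors and that the final interview is meant to show whether patients got better or worse, so direction can be read from context. Only tobacco abstinence is strictly incapable of a 5 % change; LDL and minutes of activity are continuous underneath. A difference of 5 percentage points between group proportions is another possible reading. Detailed coding of secondary endpoints is often left to a fuller document.

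Part of this stands. The intended direction is probably improvement, and the yes/no problem is absolute for one item only. But the article does not merely leave the coding open: it fixes a numerical rule and attaches it to named items. A later document would have to inherit the conflict or depart from the published rule. The percentage-point reading is not stated, and it would not suit blood pressure or HbA1c, which have no target.

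Three stronger readings are tempting and are not supported:

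- **That the 5 % cut is known to lie within measurement noise.** The documents give no within-person variability. The blood-pressure figures are conditional, concern per-patient classification rather than group means, and say nothing about LDL or HbA1c.
- **That continuous information is certain to be thrown away, with a calculable loss of power.** The Statistical analysis section also plans t or Wilcoxon tests for continuous variables, so a continuous comparison is not excluded. The usual efficiency figure for a median split does not describe a cut at 5 % change.
- **That HbA1c would come from routine records and so be available differently by arm.** The stated tests are these: "All patients will undergo blood tests with serum lipids and glucose evaluation". HbA1c is not named there, but it is listed among the before-and-after measurements, and a condensed article need not itemise assays. Nothing says that it would be taken from records.

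**Conclusion.** The point holds for the definition of the risk-factor outcome. As written, the rule counts worsening, cannot be applied to tobacco abstinence in a single patient, and classifies LDL against the protocol's own target in both directions. These conclusions follow from the text and need no assumption about the data. That the rule would set the event for logistic regression is the natural reading of the two sections together, although the continuous tests listed there leave some ambiguity.

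The blood-pressure figure of 50-69 % of unchanged patients crossing the threshold is illustrative. It rests wholly on the assumed mean of 135 mmHg and within-person SD of 7-12 mmHg, and would be much smaller with low variability.

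Only secondary outcomes are affected. The primary outcome, maintenance of CCS class I or II, does not use the rule, and the primary non-inferiority conclusion is untouched. The change is worth making, but the trial does not depend on it.

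**What to change.** Drop the 5 % rule and define the items by type.

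- **Continuous:** compare 12-month blood pressure (stating systolic, diastolic or both), LDL, and HbA1c in diabetics between arms, adjusted for the baseline value (ANCOVA), and report the difference with its 95 % CI.
- **Yes/no:** compare LDL < 100 mg/dL, tobacco abstinence and at least 150 min/week of activity at 12 months, adjusted for baseline status. The logistic regression already planned can do this, with a 95 % CI.

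This gives each outcome a direction and a scale and keeps the LDL target and the roughly 150 min/week activity level that the protocol already names. The cost is a change of wording and slightly more analysis. It uses the before-and-after measurements that the protocol already lists and needs no extra visit.

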### Statistical analysis

Continuous variables without normal distribution will be described as mean ± standard deviation or median and inter-quartile range (IQR). Categorical variables will be expressed as percentages. Comparisons between groups will be performed by Student’s *t*-test for continuous variables with normal distribution and Wilcoxon’s test for variables without normal distribution. Fisher’s exact test will be used for categorical variables. Logistic regression analysis will be used to establish the effect of the counter-referral strategy on primary and secondary outcomes at 12 months. Analysis of survival free of events at 12 months will be performed using the Cox multivariate regression and described in Kaplan-Meier survival curves. Variables with *P <* 0.10 in the univariate analyses will be included in the multivariate model. Primary outcome analysis will be according to intention to treat (ITT). Determination of sample size has taken into consideration a 10 % loss to follow-up.

Data will be analyzed in SPSS 18.0 for Windows. Statistical significance is set at *P <* 0.05.

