## Methods/design

### Study design

This randomized non-inferiority trial was designed to compare two groups: CAD patients meeting outpatient clinic discharge criteria, counter-referred from tertiary to primary care for follow-up with telemedicine monitoring (intervention group); and CAD patients meeting outpatient clinic discharge criteria with follow-up at the original tertiary care outpatient clinic (control group).

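### The non-inferiority margin sizes the trial but plays no part in its analysis: the stated tests ask only whether the groups differ

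*Protocol article*

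**What the plan says.** The Abstract and the Study design section both present a non-inferiority trial; the latter says "This randomized non-inferiority trial was designed to compare two groups". The section Study population and sample size fixes the figures: "The sample size was calculated as 140 patients in each group", "considering a non-inferiority margin of 10 % and incidence of 92 % of the main outcome". It adds that "a ß of 0.9 and an α of 0.05 (two-sided) were considered" and that "An additional 10 % margin was added to account for losses to follow-up". The primary outcome, under Outcome measures and assessment procedures, is binary: still in CCS class I or II at 12 months.

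The Statistical analysis section assigns Fisher's exact test to categorical variables and t and Wilcoxon tests to continuous ones. For the primary outcome it states: "Logistic regression analysis will be used to establish the effect of the counter-referral strategy on primary and secondary outcomes at 12 months". It also plans Cox regression and Kaplan-Meier curves for event-free survival, an intention-to-treat primary analysis and a P < 0.05 threshold. The margin is not mentioned there. Nor is a confidence interval for the difference in proportions, a test with a shifted null, or a rule for declaring non-inferiority. The Discussion expects care in the two settings to be similar, and makes future practice depend on confirming this, but gives no criterion for confirming it.

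**The concern.** Design and analysis answer different questions. The design asks whether primary care with telemedicine support is worse than the tertiary clinic by less than the margin. Fisher's test, and the usual test of a logistic coefficient, ask whether there is any difference at all. A P value of 0.05 or more on those tests does not show that a loss as large as the margin has been excluded.

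This is the primary inference of a trial meant to support moving stable patients out of tertiary care. With nothing in the analysis tied to the margin, the error rate the trial was sized to control is not controlled by any stated rule.

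**Working it through.** **Inputs.** From Study population and sample size: 140 per group, margin 10 %, success 92 %, alpha 0.05 labelled two-sided, 10 % added for losses. Assumptions: the margin is absolute (10 percentage points), 92 % applies to both groups, and the stated ß of 0.9 means 90 % power.

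**1. Reproducing the 140.** Per group, n = 2p(1 − p)(z_alpha + z_power)² / margin², with 2 × 0.92 × 0.08 = 0.1472.

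- One-sided 0.05: (1.645 + 1.282)² ≈ 8.564, so n = 0.1472 × 8.564 / 0.01 = 126.06, rounded up to 127. Adding 10 %: 127 × 1.10 = 139.7, i.e. 140. (Dividing by 0.90 instead gives 142.)
- One-sided 0.025, the equivalent of two-sided 0.05: (1.960 + 1.282)² ≈ 10.507, so n = 154.7, rounded up to 155. With losses this is 171 (× 1.10) or 173 (/ 0.90). It does not give 140.
- Superiority test of 92 % v 82 %, two-sided 0.05, 90 % power: [1.960 × √(2 × 0.87 × 0.13) + 1.282 × √(0.92 × 0.08 + 0.82 × 0.18)]² / 0.01 ≈ 236 per group before losses. It does not give 140.

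So the 140 comes from a margin comparison at one-sided 0.05. The analysis that the sample size supports is the one missing from the Statistical analysis section.

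**2. What the stated test does.** Exact binomial enumeration with 126 (140 × 0.90) and 140 evaluable per group, comparing Fisher's two-sided P with the Newcombe lower limit of the risk difference (intervention minus control):

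| True success, control v intervention | Evaluable per group | Fisher P ≥ 0.05 | 95 % limit above −10 points | 90 % limit above −10 points |
|---|---|---|---|---|
| 92 % v 82 % | 126 | 40.3 % | 2.55 % | 5.00 % |
| 92 % v 82 % | 140 | 34.6 % | 2.51 % | 4.97 % |
| 92 % v 92 % | 126 | 97.3 % | 79.6 % | 88.6 % |
| 92 % v 92 % | 140 | 97.1 % | 84.5 % | 90.8 % |

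The first two rows lie exactly on the margin, so the last two columns are false-claim rates. The Fisher column becomes a false-claim rate only if P ≥ 0.05 is read as showing similarity.

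**3. One possible result.** Control 116/126 (92.1 %), intervention 108/126 (85.7 %). Fisher P = 0.16. The difference is −8/126 = −6.3 points, standard error 3.94 points, 95 % Wald interval −6.3 ± 1.96 × 3.94 = −14.1 to +1.4. The 90 % lower limit is −12.8. The result is not significant, and non-inferiority is not shown at either level.

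**4. Scale.** Logistic regression yields an odds ratio. A 10-point loss from 92 % is (0.82/0.18)/(0.92/0.08) = 0.396. From 88 % it is (0.78/0.22)/(0.88/0.12) = 0.483, and from 96 % it is (0.86/0.14)/(0.96/0.04) = 0.256. The odds-ratio equivalent thus moves with the control rate, and the section gives neither an odds-ratio margin nor a conversion.

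**5. Power of a margin rule.** With 126 evaluable per group and 92 % in both, the standard error is √(0.1472/126) = 0.0342 and 0.10/0.0342 = 2.926. Normal-approximation power is Φ(2.926 − 1.645) = 90.0 % with a 90 % interval and Φ(2.926 − 1.960) = 83.3 % with a 95 % interval. The exact Newcombe figures are 88.6 % and 79.6 %.

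**The case against.** This is a condensed article without its analysis plan, and the choice of interval method and the wording of the decision rule are often left to that plan. The design and margin are stated, the outcome is binary, and the data will allow a margin comparison. The P < 0.05 line is generic and could fit a non-inferiority test. The 35 to 40 % figure is computed for Fisher's test, whereas logistic regression is the method named for the primary outcome. It also presumes a reading of P ≥ 0.05 that the protocol nowhere states.

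Much of this stands as a limit on the point. The percentages are conditional, and they belong to Fisher's test; the usual logistic test has the same null but would give its own figure, not computed here. The leave-it-to-the-plan argument does not remove the point. The article is not silent on the primary analysis: it names the model, the categorical test, the analysis set and the threshold, and none of these is linked to the margin on which the same article sizes the trial.

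Three stronger readings are tempting and are not supported:

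- A reader might infer that an odds ratio can never be held against a risk-difference margin. It can be converted, and a logistic model can return a risk difference by marginal standardisation. What is missing is a statement of the conversion.
- A reader might infer that a non-inferior result with P < 0.05 would be misread as failure. With 126 per group, no table has Fisher P < 0.05 against the intervention together with a 95 % Newcombe limit above −10 points. With 140 there are only two such tables (133 or 134 of 140 against 140 of 140).
- A reader might infer that the trial can never conclude non-inferiority. That is true only of the analysis as written.

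**Conclusion.** The point holds. The trial is designed and sized on a 10 % margin, but its stated analysis tests only for a difference and never compares the primary result with that margin, so as written it gives no valid basis for concluding non-inferiority. If P ≥ 0.05 on Fisher's test were read as similar, a true 10-point loss would be missed in about 35 to 40 % of trials (140 down to 126 evaluable per group), against about 2.5 % or 5 % with a 95 % or 90 % limit held to the margin.

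This rests on reading the margin as absolute, which reproduces the 140, and on 92 % success in the control group. It does not rest on any claim that the investigators intend to misread a non-significant result; the documents do not say so. The point should be settled because it concerns the trial's main conclusion, and the repair also exposes a mismatch between the stated alpha and the stated power.

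**What to change.** Make the primary analysis the risk difference (intervention minus control) in maintenance of CCS I or II at 12 months, with a Newcombe or Miettinen-Nurminen confidence interval. Declare non-inferiority only if the lower limit is above −10 percentage points, and state that the margin is absolute. If logistic regression is kept, obtain the risk difference and its interval by marginal standardisation. Keep Fisher's P and the odds ratio as descriptive.

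State the interval level and restate the sample-size paragraph to match:

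- A two-sided 95 % interval agrees with the stated two-sided alpha of 0.05, but power at 126 evaluable per group is then about 80 % (exact Newcombe) to 83 % (normal approximation). Keeping 90 % by the sample-size formula would need 155 evaluable, or 155/0.90 = 173 randomised, per group.
- A two-sided 90 % interval (one-sided 0.05) is the only reading under which 140 per group reproduces 90 % power. The alpha must then be restated as one-sided 0.05.

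The cost is one paragraph in Statistical analysis and a corrected line in the sample-size section, with no new data to collect. The real cost lies in the first option: accept the lower power or enlarge the trial. The change should be made before outcomes are compared between groups.
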